#### Acceptance and commitment therapy (ACT)

ACT utilize two main approaches to facilitate the development of psychological flexibility, such as mindfulness and acceptance as well as commitment and behavioral change. ACT session begin with building of therapeutic rapport and formulation of the case. Brief mindfulness exercise and home assignment review are also introduced at the initial stage. The remaining sessions of ACT will then focus on the use of pre-plan learning materials and exercises to facilitate didactic and experiential learning. Hence, each subsequent sessions will work on addressing the specific themes introduced by Hayes et al. (2009), such as EA, cognitive fusion, self as context, defining valued directions in life, and the commitment to action strategies to pursue their valued directions in life [9]. Home assignments in the form of behavioral practices and experiments are provided at the end of each session. The workbook provided to the respondent is based on the book “Get out of your mind and into your life” written by Hayes et al (2005) [51] and “ACT made simple” written by Harris (2009) [52]. The details of all the ACT sessions are described in S1 Appendix.

#### Mindfulness-based stress reduction (MBSR)

MBSR will be conducted as group sessions, with each session lasts for 2.5 hours, once a week for 8 weeks with another 45 minutes of home practice on daily basis. The MBSR sessions will be based on therapy format developed by Kabat-Zinn [40]. All the sessions focus on mindfulness practices, sharing of experiences with others, and didactic teaching on stress. Mindfulness practices which will be discussed include body scan exercise, and mindful breathing meditation techniques, three-minute breathing exercises, five-minute seeing or hearing exercises, bodily mindfulness in movement and mindful stretching, yoga and sitting meditation. The therapists will review feedbacks for each session, acknowledge the thoughts, feelings, and senses, examine how participants practice mindfulness, and give assignments to encourage participants to continually practice mindfulness at home. Each participant will receive a CD detailing on meditation practices and a workbook on the mindfulness practices. The details of all the MBSR sessions are described in S1 Appendix.

#### Treatment-as-usual control group

The participants in the control group will receive treatment-as-usual in which non-specific ingredients of the psychotherapeutic approach will be administered, such as psychological understanding to the management of an individual patient, identifying current problems, providing opportunities for disclosure, reassurance, and deep breathing exercise. They will be given equal amount of time and attention from the professional figure compared to the intervention groups, whereby they will also attach to an 8-session program (with one session per week for 8 weeks).

### Treatment fidelity

ACT will be conducted for the ACT intervention group by a therapist trained in ACT, who will have a trained backup therapist on standby to replace the primary therapist when necessary. Similarly, MBSR will be conducted for the MBSR group by a therapist trained in MBSR, and a trained backup therapist will be on standby to replace the primary therapist when necessary. All the study’s therapists and backup therapists will be postgraduate students in psychology who are not otherwise involved in the study. All the therapists have two-year experience of conducting psychotherapy. They will also receive training manual detailing the psychotherapy sessions for both ACT and MBSR, and they will also undergo 2 full days of brief training workshop for ACT and MBSR from the principal investigator. As for monitoring of treatment integrity, a psychiatrist and a clinical psychologist, both trained in ACT and MBSR will measure the delivery of the interventions by all the therapists in the ACT and MBSR groups independently. 15% of audio-recording of the psychotherapy sessions will be randomly selected and stratified according to therapist and the phase of intervention (early, middle or end) and then, treatment integrity assessments will be performed by using: (1) the Drexel University CT/ACT Therapist Adherence and Competence Rating Scale (DUACRS) [53] for ACT sessions and (2) the Mindfulness-Based Interventions: Teaching Assessment Criteria (MBI:TAC) [54]. Each treatment integrity assessor will assess half of the selected sessions. Finally, the interrater reliability of the two treatment integrity assessors is computed to assess the treatment integrity of all the therapists in delivering the interventions [55]. In addition, the principal investigator will discuss issues regarding the delivery of the interventions with the therapist who is inconsistent in conducting the ACT and MBSR sessions.

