### Participants

This study’s participants will be recruited from the source population. This population includes all newly diagnosed head and neck cancer patients who have been treated only with surgery or who have not yet received treatment and who are registered under the oncology and otorhinolaryngology unit of the Advanced Medical and Dental Institute (AMDI) at the Universiti Sains Malaysia (USM) or the oncology and otorhinolaryngology unit of Universiti Kebangsaan Malaysia Medical Centre (UKMMC). The study’s sample size was determined based on G-Power 3.1.9.2 for analysis of variance (ANOVA). This sample size was calculated based on continuous responses to the posttraumatic growth inventory used in the study by Labelle et al. (2015) [48] with a medium effect size (0.15) and a two-tailed alpha of 0.05. The results of this calculation indicated that the current study requires a total sample of 93 for three equal-sized groups to achieve a power of 0.8. Anticipating a drop-out rate of 30%, we estimated a total sample size of 120 respondents and 40 respondents for each group.

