### Interventions

An eight-week psychosocial intervention will be administered to participants in each intervention group (MBSR and ACT) while participants in the control group will receive treatment-as-usual. The study’s outcomes will be assessed at three times: pre-intervention (t_0_), immediately after the eight-week intervention (t_1_), and 24 weeks after the intervention (t_2_).

Both the ACT and MBSR interventions will comprise eight sessions delivered at a rate of one session per week. Each session will last for one hour. At AMDI, USM, and UKMMC, chemotherapy for head and neck cancer lasts for 8 weeks, delivered at a rate of one session per week. Similarly, radiotherapy for head and neck cancer lasts for eight weeks at these institutions. Therefore, this study’s ACT and MBSR sessions will align with participants’ chemotherapy or radiotherapy sessions to ensure that all participants attend their intervention sessions. ACT and MBSR will be provided in group settings with intervention groups of 10 participants each.

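### The fidelity plan splits the sampled recordings between two assessors, then uses their interrater reliability as the treatment integrity result; no joint rating is stated, and agreement does not measure integrity

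*Protocol article*

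**What the plan says.** The plan is in the Treatment fidelity section of the protocol article. There are two raters: "a psychiatrist and a clinical psychologist, both trained in ACT and MBSR will measure the delivery of the interventions". The sample is set next: "15% of audio-recording of the psychotherapy sessions will be randomly selected and stratified according to therapist and the phase of intervention". ACT sessions are scored with one instrument and MBSR sessions with another: "treatment integrity assessments will be performed by using: (1) the Drexel University CT/ACT Therapist Adherence and Competence Rating Scale (DUACRS") for ACT, and the MBI:TAC for MBSR.

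The division of labour follows: "Each treatment integrity assessor will assess half of the selected sessions". The section then states the statistic and its purpose: "the interrater reliability of the two treatment integrity assessors is computed to assess the treatment integrity of all the therapists".

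The article mentions no doubly rated subset, calibration set or other overlap. It names no summary of the DUACRS or MBI:TAC scores as the integrity result.

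**The concern.** Two things do not fit.

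First, an agreement statistic needs the same sessions scored by both raters. If the sample is divided between them, any difference between their scores mixes a difference between raters with a difference between sessions, and the two cannot be separated.

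Second, the stated purpose of the statistic is to assess the therapists. Agreement is a property of the ratings. Two assessors can agree perfectly that a session was poorly delivered, and they can disagree about one that was delivered well.

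Fidelity evidence matters in this trial. The primary objective compares ACT with MBSR as well as with control. The two therapies share content, since the article places mindfulness within ACT. The therapists are postgraduate students who receive a manual and a two-day workshop covering both therapies, and the Discussion says at most four will be used. Readers of an ACT versus MBSR comparison will want to know whether each therapy was delivered as intended and whether the scores that say so are consistent between raters. As written, the plan does not secure the second and names the wrong quantity for the first.

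**Working it through.** The article gives no number of recordings, overlap or reliability coefficient, so there is no stated figure to reproduce. The check is a count of what the design yields, followed by the precision that a repaired design could reach.

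**Inputs**
- Participants per arm: 40 (Participants: "we estimated a total sample size of 120 respondents and 40 respondents for each group").
- Group size: 10 (Interventions: "ACT and MBSR will be provided in group settings with intervention groups of 10 participants each").
- Sessions per group: 8 (Interventions).
- Share of recordings sampled: 15% (Treatment fidelity).
- Assessors: 2, each rating half (Treatment fidelity).
- Assumed, not stated: all groups are full and every session is recorded.

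**Recordings**
- Groups per intervention arm: 40 / 10 = 4.
- Sessions per arm: 4 × 8 = 32. Both arms: 2 × 32 = 64.
- Selected: 0.15 × 64 = 9.6, about 10. Per arm, and so per instrument: 0.15 × 32 = 4.8, about 5.
- Per assessor: 10 / 2 = 5.

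**Sessions rated by both assessors**

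Joint share = share of assessor 1 + share of assessor 2 − share rated by at least one.

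- The halves together cover the sample (natural reading): 0.5 + 0.5 − 1 = 0, so no session is jointly rated. This does not depend on the number of recordings.
- Both rate the same half: 0.5 + 0.5 − 0.5 = 0.5, so 5 sessions are jointly rated and 5 are never rated. The rated share falls from 15% to 7.5% of all recordings.
- Each draws a half independently at random: expected joint sessions = 5 × 5 / 10 = 2.5.

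The article states neither of the last two schemes.

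**Precision if all selected recordings are rated by both**

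The illustration uses a one-way ICC with k = 2 raters and an assumed ICC of 0.80.

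- F = (1 + ICC) / (1 − ICC) = 1.80 / 0.20 = 9.
- Each confidence limit is (F* − 1) / (F* + 1). For the lower limit, F* = 9 divided by the 97.5% point of F(n − 1, n). For the upper limit, F* = 9 multiplied by the 97.5% point of F(n, n − 1).
- Lower limit, n = 5: 9 / 7.39 = 1.218, giving 0.218 / 2.218 = 0.10.
- Upper limit, n = 5: 9 × 9.36 = 84.2, giving 83.2 / 85.2 = 0.98.

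The relevant n is 5, because ACT and MBSR sessions are scored on different scales. Pooling all 10 would give 9 / 3.78 = 2.38 and 9 × 3.96 = 35.6, an interval of 0.41 to 0.95, but that coefficient would mix two instruments.

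**The case against.** The strongest reply is that the article never says the halves are different. It says that the two assessors work independently and that their reliability is computed. A full protocol could contain a jointly rated subset that a condensed article omits. This stands in part: disjoint halves are an inference, though the natural one. It does not rescue the text. Working independently describes how the ratings are made, not which recordings are shared. If the shared set is the same half, half of the selected sample is never scored. The allocation and the statistic also stand in adjacent sentences that do not fit together, so this is a conflict in what is stated rather than an omitted detail.

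A reader might go further and infer that the trial will have no usable fidelity evidence, so that a null ACT versus MBSR result could not be told apart from poor or blended delivery. The documents do not support that. The sampled sessions will be scored on DUACRS and MBI:TAC, sampling is stratified by therapist and phase, and the principal investigator follows up therapists whose delivery is inconsistent. Those scores exist whether or not a reliability coefficient can be computed. What is at risk is the check that the scores are consistent between raters.

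It can also be said that the phrase about assessing integrity is loose wording after a sentence that already names proper integrity instruments. That is fair as to intent, but the only result the section names is the reliability coefficient. Finally, double rating about 5 recordings per instrument gives a very wide interval. That is correct, and it limits what the repair can deliver.

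**Conclusion.** The point holds as a flaw in the stated fidelity analysis. On the natural reading there are no jointly rated sessions, and interrater reliability cannot be estimated whatever the number of recordings. On the alternative that both rate the same half, the sample actually scored is half of what the plan promises. Under every reading, reliability is the wrong quantity to stand for treatment integrity.

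The counts of about 10 recordings in total and about 5 per instrument assume full groups of 10 and complete recording. The interval of about 0.10 to 0.98 assumes an illustrative ICC of 0.80 and a one-way model with two raters.

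The consequence is modest. Sample size, alpha and the primary efficacy analysis are untouched, and integrity scores will still be collected. The correction is worth making because it is cheap and should be settled before rating begins.

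**What to change.** Revise the Treatment fidelity section in three respects.

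1. Have both existing assessors independently rate all selected recordings, about 10 in total (about 5 ACT and 5 MBSR).
2. Report interrater reliability separately for DUACRS and MBI:TAC, with a confidence interval, as a property of the ratings only. State in advance that about 5 recordings per instrument will estimate it with low precision.
3. Name the DUACRS and MBI:TAC adherence and competence scores as the treatment integrity result.

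The cost is about 10 − 5 = 5 more recordings for each existing assessor, plus the change of wording. No new staff are needed and nothing changes in the efficacy analysis.

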### Blinding

Participants will be kept unaware of the study’s randomization into the designated groups, conducted by a research assistant who is not otherwise involved in the study and concealed in an opaque, sequentially numbered envelope. Therefore, participants will not know which group they are allocated to. In addition, the intervention groups (ACT and MBSR) as well as the treatment-as-usual control group will receive an 8-session program (with one session per week for 8 weeks) and participants in the treatment-as-usual group will also receive equal amount of attention and time from the professional figure who administer the program.

The researchers will also be “blinded” for the study since the participants’ randomized assignment into the designated groups will be conducted by a research assistant who is not otherwise involved in the study or data analysis. This project’s data collection will also be conducted by that research assistant who is not otherwise involved in the study or data analysis and who is unaware of the study’s hypotheses. Moreover, the project’s data analysis will be conducted by statisticians who are not otherwise involved in the study. A statistical analysis plan is established prior to the final unblinded of the data lock.

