## Methods/Design

### Design

The current study will conduct a multicentre, three-armed, parallel-group, double-blind RCT that is expected to run for three years.

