### Randomization

This study will use stratified permuted block randomization, stratifying trial participants according to their age (*18 to 40 years old*, *41 to 60 years old*, and *over 60 years old*) and gender (*male* and *female*). Participants will be randomized into three groups: an ACT group, an MBSR group, and a control group of patients on treatment-as-usual for intervention. Using a 1:1:1 allocation ratio and block randomization, we will randomly assign participants to the three groups. An allocation sequence will be generated via computer-generated random numbers, which will be obtained by a research assistant who is not otherwise involved in this study. The allocation sequence will be concealed in an opaque, sequentially numbered envelope.

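### The double-blind label is not met: participants attend recognisably different programmes and report their own outcomes, and the assistant who allocates them also collects the data

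*Protocol article*

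**What the plan says.** The Abstract and the Design section describe the trial as double-blind; Design has "multicentre, three-armed, parallel-group, double-blind RCT".

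The Blinding section makes three relevant statements.

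- **Participants.** After describing concealment in opaque, numbered envelopes it concludes: "Therefore, participants will not know which group they are allocated to". It adds that all three arms have eight weekly sessions and that controls get the same time and attention.
- **Allocation and data collection.** Researchers are called blinded because "randomized assignment into the designated groups will be conducted by a research assistant who is not otherwise involved in the study or data analysis". The next sentence says "data collection will also be conducted by that research assistant who is not otherwise involved in the study or data analysis", and adds that this person is one "who is unaware of the study’s hypotheses".
- **Analysis.** Statisticians with no other role in the study do the analysis, and a later unblinding is mentioned.

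The Randomization section says the sequence comes from "computer-generated random numbers, which will be obtained by a research assistant who is not otherwise involved in this study".

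**The concern.** Allocation concealment and blinding are different protections. Concealment keeps those who enrol from foreseeing the next assignment, and it ends when the envelope is opened. Blinding keeps people unaware of the assignment afterwards. The protocol offers the first as proof of the second.

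This matters because every outcome is a questionnaire about the participant's own state. The participant is in effect the outcome assessor, so awareness of the therapy received reaches the primary outcome directly. A collector who knows the arm adds a second, smaller route, through how questionnaires are introduced, explained or chased. A reader who takes double-blind at face value would credit the result with protection that the design does not provide.

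**Working it through.** The protocol gives no figure for this point to reproduce. The check sets its sections side by side.

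**1. Can participants be unaware of their programme?**

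- Recruitment process: the study's purposes and procedures are explained to patients before consent.
- ACT section: a workbook based on ACT books, with work on values, cognitive fusion and committed action.
- MBSR section: yoga, body scan and sitting meditation; "Each participant will receive a CD detailing on meditation practices and a workbook on the mindfulness practices".
- Treatment-as-usual section: non-specific support, reassurance and deep breathing.

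There is some overlap: ACT includes a brief mindfulness exercise and controls do breathing exercises. Even so, a participant who has had the procedures explained and then attends eight sessions can recognise the programme. An envelope cannot hide it.

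**2. Are the arms matched in visible duration?** The document contradicts itself.

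- Interventions section, one hour per session for both therapies: 8 × 1 h = 8 h.
- MBSR section, 2.5 hours per session: 8 × 2.5 h = 20 h. Daily home practice of 45 minutes, if done every day for 8 weeks, adds 56 × 0.75 h = 42 h.

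If the MBSR section applies and ACT stays at one hour, controls cannot match both 8 h and 20 h, and duration becomes a further visible difference. These sections must be reconciled.

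**3. Do therapists know?** Under Treatment fidelity, each programme is delivered by a therapist trained in it. They necessarily know.

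**4. Does the outcome collector know?** The Blinding section assigns participants through a research assistant and gives data collection to that same person. The stated safeguard is unawareness of the hypotheses. Unawareness of allocation is nowhere stated, and cannot hold for the person who makes the assignments. Nor can someone with both tasks be without other involvement in the study. The Randomization section describes the person who obtains the sequence in near-identical words.

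**5. Which outcomes are exposed?** The FACT-H&N, Hope Scale, LOT-R and HADS are described as self-reported or self-rated. The PTGI-SF and AAQ-II do not carry that word but are questionnaires on the respondent's own inner state. That gives one primary outcome (PTG) and six secondary ones (QoL, hope, optimism, depression, anxiety, experiential avoidance). At t1 and t2 this is 7 × 2 = 14 outcome-by-visit assessments.

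**The case against.** The strongest reply is that participants and therapists cannot be blinded when distinct psychotherapies are delivered, so this part is a matter of labelling and not a design choice that could have gone otherwise. That stands, and it is why the remedy for participants is accurate wording plus a stated limitation.

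The protocol also has real mitigations. Controls receive an eight-session programme with matched attention, so this is not a comparison with no contact. The collector is said not to know the hypotheses. Participants may not know which programme is expected to do better. These points reduce expectation and prompting bias, but none of them makes anyone unaware of the arm.

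A reader might infer more than the document supports:

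- *That the assistant's dual role is what unblinds the outcomes.* With self-completed scales the participant's own awareness matters most. Splitting the roles does not remove it.
- *That controls receive no materials.* The control section is silent on this.
- *That the sequence is certainly obtained by the same assistant who collects data.* The wording is nearly the same in both sections, but identity is not stated.
- *That the analysis is unblinded too.* The Blinding section points the other way.

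**Conclusion.** The point holds. The design does not have the double-blind property claimed in the Abstract and under Design, and the inference about participants in the Blinding section does not follow from its premise. Participants and therapists are not blinded. As written, the outcome collector is not blinded either. Blinding of the statisticians may stand.

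All seven outcomes at both post-baseline visits are exposed to possible bias. It would go too far to say that they are biased: neither size nor direction can be derived from the document. The conclusion rests on two readings: that the assistant in the data-collection sentence is the one who makes the assignments, as the wording says, and that the PTGI-SF and AAQ-II are completed by participants. The correctable defect in conduct is narrow (one person allocates and collects); the rest is correction of what is claimed.

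**What to change.** 1. **Separate the roles (Randomization and Blinding sections).** Give sequence generation, list-holding and envelope-opening to an existing team member who has no outcome contact and no auditing role. The clinical trial coordination unit is a poor choice, because under Support and ethics it monitors and audits the trial and would then audit a process it runs. Have the t1 and t2 questionnaires collected by someone with no access to the sequence or the allocations. If the present assistant has obtained the sequence, moving only the envelope-opening would not make that person blind.
2. **Replace the label in the Abstract and under Design.** State that the outcome collector (once the roles are split) and the statisticians are blinded, and that participants and therapists are not.
3. **Delete the inference in the Blinding section** that participants will not know their group. Keep the envelopes as a description of allocation concealment, and the matched attention as a mitigation.
4. **Name unblinded self-report as a limitation.**
5. **Reconcile the session lengths** in the Interventions and MBSR sections, since the equal-time argument depends on them.

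The cost is a minor reassignment of tasks, wording changes and a less favourable blinding label. Sample size and visits do not change.
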